## Abstract

**Background:**

Existing studies have unequivocally demonstrated that parents of children with autism spectrum disorder (ASD) experience various stressful daily life events and suffer from psychological distress. Mindfulness level is found to be an effective buffer between parents’ appraisal of stress life events and psychological distress. However, the mechanism behind the function of mindfulness is unclear, and traditional mindfulness-based intervention (MBI) in experimental settings is not tailored to personal real-life needs. This study proposes to conduct a randomized controlled trial (RCT) to examine the effectiveness of MBI delivered by ecological momentary intervention (EMI) and assessed by ecological momentary assessment (EMA) in changing participants’ cognitive appraisal of stressful life events and thus reducing the psychological distress of parents of children with ASD.

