There are several benefits of using EMI and EMA. First, the application of EMI enables researchers to reach large populations easily, rapidly, and cheaply [40]. Secondly, using EMI can modify the contents of intervention based on individual and contextual factors that vary across time and to fit individual needs and backgrounds. Thirdly, By using EMI, participants can practice the skills and exercises in real-life settings that fit their day-to-day routine, reducing the burden on parents of children with ASD to change their daily schedule [40]. Lastly, using EMA enables researchers to obtain information with maximized ecological validity and to track behaviors and experiences change over different periods and contexts [41].

Existing research has offered clinical evidence supporting the effects of EMI and EMA in promoting healthy behavior and psychological well-being [40, 42]. Yet, the literature search on PubMed found no prior study examined the effects of MBI using EMI for parents of children with ASD. Only one study protocol was proposed to explore mindfulness intervention and EMI to decrease adolescent stress and anxiety [43]. The knowledge in filling the above research gaps is essential for examining the mechanism between life events, cognitive appraisal, psychological distress, and methods for reducing the psychological distress of parents of children with ASD.

This study aims to develop and implement the MBI using EMI and EMA platform (EMI/A-MBI) and to assess the effectiveness of this newly developed EMI/A-MBI on reducing psychological distress in parents of children with ASD. Specifically, we aim:

to identify the daily sources of depression, anxiety, and stress in parents of children with ASD and what are the protective factors for resilience;(comparison of the intervention and control group) to evaluate the effectiveness of EMI-MBI in improving the psychological well-being of parents of children with ASD;(within the intervention group) to explore whether the intensity and frequency of mindfulness practice moderate the participants’ cognitive appraisal of daily life events and their psychological distress and mental well-being.

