### Research hypotheses

The research hypotheses of this proposed study include the following:

The intervention group would show a significant reduction in depression, anxiety, and stress than the control group right after intervention and during follow-up.The intervention group would significantly increase life satisfaction and empowerment more than the control group right after intervention and during follow-up.The intensity and frequency of mindfulness practice would moderate the relationship between participants’ cognitive appraisal of daily life events and psychological distress and mental well-being in the intervention group.

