## Methods

### Trial design

This research adopts a parallel-armed, randomized controlled trial (RCT) design. The intervention group will receive a combination of (1) a time-based system-triggered EMA, which will collect participants’ sources and status of depression, anxiety, and depression in daily life; (2) EMI-delivered MBI, and (3) a follow-up survey of long-term effects of EMI/A-MBI. The participants will complete a baseline questionnaire and then participate in EMI via a smartphone application (App) for eight consecutive weeks and receive the daily exercise prompts. The EMA will include questions about self-reported depression, anxiety, and depression. After the 8-week EMI/A-MBI, the participants will be invited to complete a post-experimental survey with similar questions in the baseline questionnaire. Two months after completing the EMI/A-MBI, participants will be contacted to complete a telephone follow-up survey with similar questions in the baseline questionnaire. The control group will receive the longitudinal survey exactly the same as the intervention group and 8-week mindfulness-based short messages sent by the research team on a daily basis. The messages will contain audio-based instructions for mindfulness-based practice, which will be the same as the intervention group. The SPIRIT schedule of enrolment, interventions, and assessments can be found in Fig 1 and the flowchart of the design can be found in Fig 2. (The SPIRIT checklist can be found in S1 File).

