*Psychological Empowerment Scale for parents of children with a disability (PES)* [56]. It is a 32-item questionnaire on a 5-point scale (1 = strongly disagree to 5 = strongly agree) with four underlying sub-scales: (a) attitudes of control and competence, (b) cognitive appraisals of critical skills and knowledge, (c) formal participation in organizations, and (d) informal participation in social systems and relationships (57). This scale showed high-reliability coefficients (0.90–0.97) [56].

Parents’ life events will be prompted daily in the EMI/A app, and questions will be modified from the systematic review that summarizes the risk and protective factors of psychological distress [57]. The shortened version of the scale measuring mindfulness and psychological distress will be embedded in EMI/A and prompt out every day for future analysis.

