To answer the third question, structural equational modelling will be adopted to examine the pathways of the relationship between daily life events, cognitive appraisal, and psychological distress. Moderation analysis will also be used to explore the effects of mindfulness. The model will be adjusted for the participants’ role of mother or father. Bootstrapping with size 10,000 will be used to estimate the 95% confidence interval of the parameters. After checking data distribution normality, several fit indices will be served as the judgment of the fit of the model. A non-significant chi-square (X^2^) is desired, but the test is sensitive to erroneously reject a correct model when the sample size is not large enough [61]. The Comparative Fit Index (CFI) and the Non-Normal Fit Index (also known as the Tucker-Lewis Index, TLI), ranging from 0.00 to 1.00, with higher values representing better fit, will be adopted [62]. The standardized root-mean-square residual (SRMR) and root mean square error of approximation (RMSEA) will be used to detect model misspecifications, with values below 0.08 considered desirable [62]. The indirect effect of the model will be checked with the Sobel test.

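### The Abstract sets out to test whether the app changes cognitive appraisal and so lowers distress, but no between-arm comparison of appraisal is stated

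*Protocol article*

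**What the plan says.** The Abstract (Background) says the randomised trial will examine how effective the app-delivered intervention is "in changing participants’ cognitive appraisal of stressful life events and thus reducing the psychological distress of parents of children with ASD".

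The aims stand at the end of the Introduction section on EMI/A. The one between-arm aim is a "comparison of the intervention and control group) to evaluate the effectiveness of EMI-MBI in improving the psychological well-being of parents". Appraisal appears in the next aim, which reads "within the intervention group) to explore whether the intensity and frequency of mindfulness practice moderate the participants’ cognitive appraisal of daily life events". Research hypotheses follows the same split. Hypothesis 1 says "The intervention group would show a significant reduction in depression, anxiety, and stress than the control group"; hypothesis 2 concerns life satisfaction and empowerment; hypothesis 3, on moderation by practice, is the only one to mention appraisal and is limited to the intervention group.

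Outcomes names DASS as primary, and life satisfaction (SWLS) and empowerment (PES) as secondary. A 28-item Cognitive Appraisal of Health Scale is described among the measures, but the text gives neither arms nor time points for it. Trial design states: "The control group will receive the longitudinal survey exactly the same as the intervention group".

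In Data analysis, the mixed model serves the first two questions and adjusts for baseline DASS. For the third question, structural equation modelling is planned "to examine the pathways of the relationship between daily life events, cognitive appraisal, and psychological distress", with bootstrap intervals and a Sobel test of the indirect effect.

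**The concern.** The stated purpose is causal and has two steps: the app shifts appraisal, and that shift lowers distress. Randomisation can support the first step directly and supplies a randomised exposure for the second. The plan does not state that it uses randomisation for either.

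Where appraisal is analysed, the comparison is between parents in the app arm who practise more and those who practise less. They chose how much to practise, and may differ in distress, free time or motivation. An association found there cannot show that being allocated to the app changed appraisal.

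The practical risk lies in reporting. A between-arm DASS difference could be set beside a within-arm appraisal association, and the two read together as evidence of mechanism, with no randomised evidence linking them.

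**Working it through.** No figure in the plan belongs to this point. The check follows one construct, cognitive appraisal, through the article.

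| Place | Between-arm content | Is appraisal named? |
|---|---|---|
| Abstract, Background | Purpose of the randomised trial | Yes, as the route to lower distress |
| Aims, between-arm aim | Psychological well-being | No |
| Aims, practice and appraisal | None; intervention group only | Yes, as moderation by practice |
| Hypothesis 1 | Depression, anxiety, stress | No |
| Hypothesis 2 | Life satisfaction, empowerment | No |
| Hypothesis 3 | None; intervention group only | Yes, as moderation by practice |
| Outcomes | DASS; SWLS and PES | No |
| Data analysis, mixed model | Treatment group, and group by time | No; baseline DASS is the named baseline covariate |
| Data analysis, structural equation model | No treatment-arm term named | Yes |

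Appraisal is therefore in the objective, drops out of everything described as a comparison of arms, and returns only under the third question. The structural equation paragraph does not itself say that it is confined to one arm. That follows from its tie to the third question, which the aims and hypotheses place within the intervention group.

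**Could the trial support a comparison by arm?**

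Inputs: 536 participants required, 20% dropout and 80% power (Sample size); two-sided 5% level (Data analysis).

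- The plan's inflation reproduces: 536 / (1 − 0.20) = 670, or 335 per arm.
- Completers per arm: 536 / 2 = 268.
- Detectable standardised difference for a simple two-group comparison: (1.960 + 0.842) × √(2/n).
- n = 268: 2.802 × √(2/268) = 0.242 SD.
- n = 335 (no dropout): 2.802 × √(2/335) = 0.216 SD.

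These figures concern the total effect of arm on appraisal. They are not power for the indirect effect through appraisal to distress, which would need assumptions about the appraisal–distress path that the article does not give.

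**The case against.** The strongest reply is that the Abstract sentence is background. The operative aims keep appraisal as an exploratory, within-arm question, the outcomes and analyses follow those aims, and the Conclusion describes the aim as alleviating distress without mentioning appraisal. On this view the smallest remedy is to reword one sentence. That is fair, and rewording is offered below as an alternative. It does not remove the mismatch: the Abstract presents the appraisal pathway as what the randomised trial examines, and the Discussion again names mechanism as an aim.

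Several stronger readings are tempting and are not supported:

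- A reader might infer that arm is excluded from the pathway model. The text names neither a restriction nor an arm term; the restriction is an inference from the third question. Detailed model specification may also sit in an analysis plan that is not shown.
- A reader might infer that appraisal is not measured in controls. The control arm receives the same longitudinal survey, and Figs 1 and 3, which are not shown, may place the scale there. That would settle measurement, not the absent comparison.
- A reader might infer that the article contradicts itself on daily content, because the Abstract has the EMA covering appraisal while the measures section says "The shortened version of the scale measuring mindfulness and psychological distress will be embedded in EMI/A and prompt out every day". That sentence, with the daily life-event prompts beside it, is not presented as a complete list. The two places need only be checked for consistency.
- A reader might infer that mediation with arm as exposure would remove confounding. It would not: appraisal itself is not randomised. Both arms also receive mindfulness instruction, so an arm contrast speaks to app delivery rather than to mindfulness in general.

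**Conclusion.** The point holds as a mismatch between the stated objective and the stated comparisons. The Abstract promises a randomised examination of change in appraisal leading to lower distress, and no between-arm comparison of appraisal is stated in the aims, hypotheses, outcomes or mixed model. Which constructs are outcomes, and which contrast answers the objective, are choices the article itself makes, so this is more than detail left to a later document.

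The effect is confined to the mechanism claim. The primary between-arm DASS inference is untouched. The 0.24 SD figure shows only that a comparison of appraisal is feasible with the planned sample; it does not measure harm. It assumes 268 analysed per arm and a simple two-group test.

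The conclusion rests on reading the third question in Data analysis as the practice-and-appraisal aim and hypothesis 3. If the pathway model were meant to span both arms, the article would still need to say so and to give arm a place in it.

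**What to change.** Preferred change:

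1. Name the Cognitive Appraisal of Health Scale as a secondary, mechanistic outcome in the baseline, post-test and 2-month follow-up survey of both arms.
2. Compare it by arm with the planned mixed model, adjusting for baseline appraisal.
3. Fit the indirect-effect model with randomised arm as exposure, post-test appraisal as mediator and 2-month DASS as outcome. Adjust for baseline appraisal and baseline DASS, use bootstrap intervals, and report it as exploratory because the appraisal–distress path is not randomised. The within-arm practice analysis can stay alongside as a separate exploratory question.

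Alternative: keep the analyses as they are and narrow the Abstract's objective to what is tested, namely the effect on distress and well-being, with appraisal explored within the app arm.

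The preferred change costs one more secondary outcome and, if the scale is not already in the control arm's survey, 28 more items there. Extra daily appraisal prompts are not needed: they would sit in an app that controls do not have, so they could not inform a comparison of arms.

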**Method:**

The proposed study will recruit 670 parents of children with ASD and randomly assign them to the intervention and control groups (335 in each group). Participants in the intervention group will install the EMI/A app on their smartphones. In the app, participants can receive practice prompts daily, browse and practice different mindfulness exercises in the intervention library at any time, talk to a virtual counselor (chatbot) when feeling stressed, complete EMA on the cognitive appraisal of life events, and receive the log of change of psychological status daily. Participants in the control group will only receive audio-based standardized mindfulness practice instructions three times per week. The effects of MBI will be assessed based on the EMA data, right after the intervention and at the 2-month follow-up. The primary outcome will be participants’ psychological distress measured by the depression anxiety stress scale. The secondary outcomes will include participants’ subjective well-being, measured by the satisfaction with life scale, and level of resilience, measured by the psychological empowerment scale. Multilevel structural equational modelling will be applied to examine the pathways of the relationship between daily life events, cognitive appraisal, and psychological distress.

**Discussion:**

The potential benefit of the proposed study is to increase the psychological well-being of parents of children with ASD, and the method may extend to participants suffering from other psychological issues in the future.

**Trial registration:** This trial has been registered on clinicaltrials.gov with the ID of NCT05746468.

## Introduction

### The burden of parents of children with ASD

Autism spectrum disorder (ASD) is defined as a group of complex neurodevelopmental disorders, including autism, Asperger syndrome, pervasive developmental disorder not otherwise specified (PDD-NOS), and other relevant symptoms and conditions [1]. According to a most updated systematic review, the prevalence of ASD among children aged 4 and 8 years in the United States was 1.70 and 1.85 percent, respectively, while the prevalence in Europe ranged from 0.38 to 1.5 percent [2]. Another meta-analysis reported a pooled prevalence of ASD of 0.27% (95% CI: 0.19–0.35%) in Mainland China, Hong Kong, and Taiwan [3]. The General Household Survey in Hong Kong conducted in 2019 and 2020 by the Census and Statistic Department reported that the prevalence rate of autistic spectrum disorder (ASD) among the local population below 15 is estimated at around 1.4% [4].

To take care of children with ASD, parents may suffer from different hardships. A most recent meta-analysis reported that around 31% (95% CI: 24–38%) and 33% (95% CI: 20–48%) of parents of children with ASD suffer from depression and anxiety, respectively [5]. In the Chinese context, where special education service organizations are limited [6], parents have to make much more effort to educate, coach, and support their children and prepare the independent living of their children with ASD compared with other parents [7]. Families of children with ASD may experience more parenting stress than families of children with other disabilities [8]. Parental psychological distress may also reduce the effectiveness of early teaching interventions on their children and increase children’s behavior problems [9].

### Sources of the psychological distress among parents of children with ASD

Commonly, parents of children with ASD may face objective burdens, such as disturbed family relationships, constraints in social, leisure, and work activities, financial difficulties, and subjective burden, such as loss of hope, dreams, and expectations, and embarrassment in social situations [10]. A recent systematic review of 24 studies conducted with Chinese parents with children of ASD summarized four main categories of potential life events of parental stress, including (i) cultural factors derived from Confucianism, which mainly lead to the public’s supernatural etiological beliefs and public stigma toward ASD [11]; (ii) parents’ own psychopathological symptoms and autistic traits before their child with ASD was born [12]; (iii) the severity of children’ symptoms of problem behaviors [13]; and (iv) caregiver burden, including physical, psychological, financial, social and time burden [14].

While these four major categories of life events were found to be related to the psychological distress of parents, there was also evidence that parents would cultivate and develop resilience from these factors. A qualitative interview study with Chinese parents of children with ASD suggested that parents would improve their moral character to achieve inner peace and mental health based on Confucianism teaching [15]. Chinese culture’s collectiveness also helped parents seek family and social support, and this support significantly alleviated the psychological distress of parents.

### The transaction theory of stress and coping

The transaction theory of stress and coping [16] provided the theoretical framework for comprehending why stressful life events would behave differently in different parents of children with ASD under similar circumstances, as well as why parents would develop resilience from stressful life events.

Based on the transactional theory, two kinds of cognitive appraisals are identified: primary and secondary appraisals. Primary appraisal refers to individuals’ judgment of whether an encounter is irrelevant, benign-positive, or stressful. If the individual adopts the stressful appraisal, it can be perceived in four forms, including harm/loss (damage already exists), threat (anticipated harms or losses), challenge (events that hold the potential of mastery or gain), and irrelevant [17]. Secondary appraisal denotes individuals’ judgment concerning what might and can be done. It includes an evaluation of whether a given coping option will accomplish what it is supposed to, that one can apply a particular strategy or set of strategies effectively, and an evaluation of the consequences of using a specific strategy in the context of other internal and/or external demands and constraints [16, 17].

Researchers have found that positive reappraisal comes from positive beliefs, optimism, parents’ cognitive reframing of life events, emotional acceptance and understanding, and adaptability toward having a child with ASD served as coping strategies to deal with psychological distress in Chinese parents of children with ASD [18].

### Mindfulness-based intervention (MBI) and cognitive appraisal of daily life events

According to the transaction theory, the shift of individuals’ cognitive appraisal from threat to positive involves the process of metacognition, which is a form of awareness associated with mindfulness [19]. Originated from Buddhism, mindfulness, defined as “the awareness that arises from paying attention, on purpose, in the present moment and non-judgmentally” [20], was adopted in psychological intervention by John Kabat-Zinn and its effectiveness in improving psychological well-being has been approved by different meta-analysis [21, 22].

According to Garland [23] and his Mindful Coping Model [19], mindfulness facilitates participants to transit from stress appraisals into the non-evaluative state of mindfulness, which would interrupt participants’ automatic emotional reactions and broaden participants’ scope of attention to encompass previously ignored contextual information [24]. Subsequently, when participants’ habitual responses get disrupted, they will be able to access a broader set of information from which novel situational appraisals can be generated [24]. In a nutshell, mindfulness in this process enhances cognitive flexibility and leaves participants the space for selecting adaptive reappraisals and encouraging productive re-engagement with stressful life events [24].

On the one hand, mindfulness practice may facilitate positive reappraisal, i.e., after practicing mindfulness, individuals would re-construct stressful events as benign, beneficial, and/or meaningful [25] and further lead to reduced distress and improved mental health outcomes [26]. On the other hand, the self-compassion cultivated from mindfulness practice would alter individuals’ secondary appraisal and function as a coping strategy for stress reduction [27]. After recurrent engagement of the mindful reappraisal process, the participants’ neuroplasticity and certain brain regions may thus be altered for top-down emotion regulation and positive affectivity. Gradually, mindfulness can function as a transformational practice for replacing maladaptive cognitive habits with healthy and adaptive ones [28]. (The framework can be found in S1 Fig).

